### The modeling phase

The modeling phase will be conducted through a qualitative approach:Semi-structured face-to-face interviews to explore hospice nursing staff members’ experiences and their role in implementing a nurse-led intervention focused on QoL measurementFocus groups with nursing staff members to explore their perspective about a draft version of the INFO-QoL received a week before the scheduled focus group sessionsA questionnaire survey to assess staff knowledge on QoL in PC. The questionnaire was developed according to relevant QoL literature. An academic working group of experts in PC was set up with the aim of developing the questionnaire, because a measure to gather information from PC staff about their knowledge on QoL issues in PC area did not exist. Four academic members from the University of Genoa (Italy) and the Trinity College of Dublin (UK) discussed and developed the questionnaire. The Nursing Role Effectiveness Model [18] was used to guide the development of the questionnaire. The model is based on the structure-process-outcome model of quality of care [19]. For item generation, the structure component comprehends nurses’ knowledge on quality of life in PC, the process component includes the role of nurses in PC and specifically QoL assessment-related activities, and finally, the outcome component was conceptualized as patient QoL. Sources used for item generation include a comprehensive review of the published literature, the quality of life [20], and the Outcome Measurement in Palliative Care—The Essential [7]. Guided by the conceptual framework, items were selected and assembled according to Dillman’s techniques for questionnaire construction [21, 22]. Content validity was systematically assessed and quantified according to the process described by Lynn [23]. Twenty-six international experts were invited to take part in a QoL expert panel, and 14 agreed to participate. Each of them received an email to explain the objective of the project, a structured procedure for the evaluation of content validity, and a link to the online evaluation of the draft version of the questionnaire consisting of 25 items. Each expert was invited to rate independently the relevance of each item using a four-point Likert scale (1: not relevant; 2: somewhat relevant; 3: quite relevant; 4: very relevant). The Content Validity Index (CVI) was computed for each item on a scale (I-CVI), as well as for the overall scale (S-CVI). For each item, the I-CVI was computed as number of experts giving a rating of either 3 or 4, divided by the total number of experts. The items that had I-CVIs of 0.78 or higher were retained [24]. Of the 25 items, eight were deleted and three were revised and included in the questionnaire. The final version of the INFO-QoL questionnaire was made up of 17 items with a S-CVI/Ave of 0.81 computed using the averaging method [24].

The results of the questionnaire survey will be used to inform the QoL education bundle as a component of the intervention (Component 1 of the INFO-QoL—Table 2).

As a result of this phase, the intervention will be modeled and linked to a new local procedure.

### The exploratory trial (assessing feasibility and piloting method)

As the INFO-QoL is being implemented throughout the unit and it will be difficult to deliver the intervention randomly to some patients but not to others, the feasibility stage will have a quasi-experimental non-equivalent comparison group before/after design. Although randomized controlled trials represent the gold standard, and quasi-experimental designs have a weakened confidence in making causal assertions that the results occurred because of the intervention, quasi-experimental designs can also provide useful information to establish whether (and to what extent) an intervention is effective. A non-equivalent comparison group design is the strongest of the quasi-experimental designs and can provide good evidence for nursing practice. Quasi-experimental designs are more feasible and more commonly conducted for nursing studies in clinical settings. This design will enable the researcher to pilot the components and methods and the feasibility of the INFO-QoL, in order to assess its acceptability in practice and determine whether the INFO-QoL is delivered according to the study protocol. It will also offer the opportunity to determine potential effectiveness of the INFO-QoL in improving patient QoL.

To partially address selection bias, the INFO-QoL described in Table 2 will be introduced randomly into unit 1 (intervention unit), while patients and staff in unit 2 (comparison unit) will continue with traditional clinical practice. By gathering pre-test data, we can compare the equivalence of the two groups on antecedent variables before introducing of the independent variable [25]. The study will inform methods for the future phase 3 trial in determining sample size and the power of the trial, recruitment, follow-up, and suitability of measures. For the purpose of this study, the type and quality of care delivered by sites will not be assessed: it will be assumed to be at least comparable between the two hospice units.

### Randomization

The unit of randomization is the hospice unit. To prevent performance bias before randomly allocating the experimental intervention in one of the two units, the collection of pre-test data will occur within a three-month period in both units before making any change. Subsequently, to reduce the selection bias, the INFO-QoL will be implemented randomly in “unit 1” (intervention unit), while patients and staff in the “unit 2” (comparison unit) will continue with the standard clinical practice.

Randomization will be performed independently by using a computer-generated sequence. The randomization procedure will be centralized and managed by an independent statistician at the coordinating center of the study. All study investigators, personnel, and participants will be unaware of the randomization procedure.

### Sample size

According to Cocks and Torgerson [26], this pilot trial needs a sufficient sample size, so that if our observed difference between the two groups, in the pilot trial, is zero, then the upper confidence limit will exclude the estimate that is considered “clinically significant” in the planned definitive trial. We will consider a small effect size of 0.3 and choose a confidence of 80% (that will satisfy the need for reasonable certainty for trial decision-making but would be small enough to ensure a study within a reasonable budget and timeframe). A sample size of 17 patients for unit/period produces a one-sided 80% confidence interval with a distance from the difference in means to the one-sided limit that is equal to 0.200 when the estimated standard deviations are 1.00 and 1.00. A 30% attrition rate based on rates identified in a recent systematic review [27] will lead to the inclusion of 6 additional patients for a total of 23 patients unit/period.

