### Study population

The study will be conducted on a convenience sample of two hospice units of the urban district of Genoa in the north of Italy: the Gigi Ghirotti Bolzaneto Hospice is a 12-bed nonprofit hospice (Gigi Ghirotti Hospice—Association for Research and Treatment of Pain and Palliative Care), and the Maria Chighine Hospice is a 12-bed public hospice (IRCCS AOU San Martino—IST—Teaching Hospital and Cancer Research Centre). In both of these hospice units, healthcare professionals were educated and trained in PC and communication in end-of-life care and are using the Liverpool Care Pathway [16]. According to the definition of the European Association for Palliative Care, “they admit patients in their last phase of life when treatment in the hospital is not necessary and care at home or in nursing home is not possible” [17]. The National Health System covers all or part of the costs of the care for the public and nonprofit hospice, respectively. The hospice staff of the Ghirotti Hospice includes 1 physician, 10 nurses, and 6 nursing assistants, and the Maria Chighine Hospice includes 3 physicians, 12 nurses, and 7 nursing assistants.

The sample will consist of all the PC team members within the two hospices during the modeling and feasibility phase. During the 6-month period of the feasibility phase (pre-test = 3 months; post-test = 3 months), all adult cancer patients newly admitted to the hospice units will be invited to participate in the study and they will be included after giving their informed consent. Patients too ill to receive the intervention or unable to give informed consent either due to cognitive impairment or because they are unable to understand Italian will be excluded.

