#### Potential effectiveness

QoL will be assessed by collecting data before (period I: 3 months) and after (period II: 3 months) the intervention and comparing QoL scores in the intervention and comparison unit using the Italian version of the Palliative Outcome Scale (POS). The QoL assessment will be performed within day 3 (T0) from admittance, on day 8–10 (T1), and then on day 15 (T2). To reduce detection bias, a trained research assistant—who will be blind to intervention or comparison status of the unit—will administer the POS to patients in the comparison unit. Staff will receive full disclosure of the study purpose. This outcome measure has been originally validated in advanced cancer patients in the UK. Cronbach’s alpha for internal consistency was 0.65 and kappa for reliability ranged from 0.8 to 0.62. The POS includes ten items on physical, psychological, and spiritual dimensions. Responses to each of the ten questions range on a scale from 0 to 4. A score of 0 indicates “not a problem at all” and 4 indicates “overwhelming” for the patient. The completion time is 7 min [30]. The psychometric properties of the Italian version of the POS were acceptable, Cronbach’s alpha coefficient was 0.65, and intra-class correlation coefficient was 0.72 [31].

Demographic patient information will be collected, including age, gender, education level, marital status, primary cancer site, and length of time since diagnosis. We assume that if patients are admitted to hospice with a primary diagnosis of cancer, they will all have advanced stage cancer.

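### The sample size paragraph does not say which contrast its precision refers to: 17 per unit and period excludes 0.3 SD for a post-period unit comparison but not for the before-after contrast, and the printed 0.200 fits neither

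*Protocol article*

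**What the plan says.** The Sample size section sets the criterion that "if our observed difference between the two groups, in the pilot trial, is zero, then the upper confidence limit will exclude the estimate" regarded as clinically important for the definitive trial. It fixes the inputs with "We will consider a small effect size of 0.3 and choose a confidence of 80" per cent. It then reports that "A sample size of 17 patients for unit/period produces a one-sided 80% confidence interval" whose distance from the difference in means to the limit is "equal to 0.200 when the estimated standard deviations are 1.00 and 1.00". Attrition raises 17 to 23 per unit and period.

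The section on the exploratory trial says that "the feasibility stage will have a quasi-experimental non-equivalent comparison group before/after design". The effectiveness outcome is described thus: "QoL will be assessed by collecting data before (period I: 3 months) and after (period II: 3 months) the intervention and comparing QoL scores"; this covers both units. Under Study population, over the two three-month periods, "all adult cancer patients newly admitted to the hospice units will be invited to participate in the study", so the patients in period II are in essence different people from those in period I.

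**The concern.** The stated inputs (one difference, two standard deviations) describe a comparison of two independent means. The design has four cells: two units by two periods. Only one unit receives the intervention, so allocating it at random between two units cannot balance them. The article also says that the care given at the two sites will not be assessed and is assumed comparable. The pre-test period is therefore the only source of data that can remove a standing difference between the hospices. An estimate that uses it is a difference of two differences, which has twice the variance of a single difference at the same number per cell.

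The study is meant to inform the size and power of a phase 3 trial. If the precision is read as applying to the before-after contrast, an observed zero would be taken to exclude 0.3 SD when the limit still lies beyond it. A reader who relies on the printed 0.200 would be further off still.

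**Working it through.** **Inputs.** From the Sample size section: 17 evaluable patients per unit and period, SD 1.00, one-sided 80% confidence, effect to exclude 0.3 SD, stated distance 0.200. From the design, Study population and Potential effectiveness sections: two units, two periods, new admissions in each period, hence four cells treated as independent. The one-sided 80% quantile is z = 0.842; the Student t values are slightly larger.

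**1. The plan's own figure, as a two-group difference.** Distance = t × √(2/n).
- n = 17, 32 df: 0.853 × √(2/17) = 0.853 × 0.343 = 0.293 (0.289 with z).
- n = 16 gives 0.302 with t. So 17 is the smallest n with a t-based limit within 0.3, and the 17 reproduces as a two-group calculation against 0.3.

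**2. The printed distance of 0.200.** Two groups of 17 with SD 1.00 give 0.29, not 0.200.
- Smallest n with 0.842 × √(2/n) ≤ 0.200: n = 2 × (0.842/0.200)² ≈ 35.4, so 36 per group.
- A figure near 0.200 (0.204 with z) arises only for a single sample of 17, or for 34 per unit with both periods pooled. Neither is a contrast that the article describes.

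**3. Change in the intervention unit minus change in the comparison unit.** Distance = t × √(4/n).
- n = 17, 64 df: 0.847 × √(4/17) = 0.847 × 0.485 = 0.411 (0.408 with z).
- Confidence with which an observed zero excludes 0.3: 0.3/0.485 = 0.618, and P(t₆₄ < 0.618) = 0.731.
- If all 23 recruited patients per cell were evaluable: 0.353 with t.
- Number needed for this contrast, unadjusted, to reach 0.3: 32 evaluable per cell (0.299), which is 128 in all.

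**4. Sensitivity to adjustment for the T0 POS.** Distance = 0.411 × √(1 − r²), where r is the T0–T2 correlation. The documents give no value, so r is an assumption.

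| r | Limit at 17 per cell (SD) |
|---|---|
| 0.5 | 0.356 |
| 0.6 | 0.329 |
| 0.7 | 0.294 |

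The limit falls below 0.3 only from r of about 0.68.

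**5. Sensitivity to correlation within a unit and period.** Distance = z-based limit × √(1 + 16 × ICC). The ICC is also an assumption.

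| ICC | Post-period comparison (SD) | Before-after contrast (SD) |
|---|---|---|
| 0 | 0.289 | 0.408 |
| 0.01 | 0.311 | 0.440 |
| 0.05 | 0.387 | 0.548 |

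**The case against.** A reader might infer that the trial's effect measure is a difference in differences and that 17 per cell therefore simply fails. The article does not support that. No section names the contrast, and several places fit a two-group comparison:
- The primary hypothesis sets patients of staff who have implemented the intervention against patients of staff giving usual care.
- The Sample size section speaks of two groups.
- The only role stated for the pre-test data is to check that the units are equivalent.
- The abstract's 46 patients during implementation equal 2 × 23.

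On that reading 17 per unit does exclude 0.3. This stands, and it is why the point is that the contrast is not stated. It does not settle the matter. The effectiveness section collects scores before and after in both units, and the sample size is set per unit and period. A post-period comparison leaves the whole unit difference in the estimate.

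A reader might also infer that the criterion is a binding rule for going on to phase 3. The article uses it to choose the sample size of a feasibility study and makes it no formal decision rule.

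Two further objections hold. The analysis model is properly left to an analysis plan, so its absence here is not at issue. Adjustment for T0 is no clean rescue: T0 is taken within day 3 of admission, when staff in the intervention unit are already trained in period II, and the POS measurement in that window is itself part of the intervention. T0 may already carry some of the effect.

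**Conclusion.** The point holds as a mismatch between the sizing and the design. One precision statement for a two-group difference is attached to a four-cell before-after design. At 17 per cell it meets the 0.3 criterion under one contrast (about 0.29 SD) and misses it under the other (about 0.41 SD, about 73% confidence). The printed 0.200 is wrong for two groups of 17 on either reading, and that conclusion needs no assumption about the contrast.

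The 0.41 rests on independent patients in each cell, SD 1.00, no covariate adjustment and no unit-by-period variation. With one unit per arm, such variation cannot be separated from the intervention effect, so 0.41 is a best case. The 0.29 for the post-period comparison rests on the same independence.

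**What to change.** In the Sample size section:
- Name the effect as the unit-by-period contrast: the change in the intervention unit minus the change in the comparison unit.
- Replace 0.200 with about 0.41 SD at 17 evaluable patients per cell, and drop the claim that 0.3 is excluded for that contrast.
- Say that 0.41 assumes independent patients and no unit-by-period variation, and is therefore a best case.
- If wanted, give adjustment for the T0 POS as a sensitivity analysis, with limits of 0.36 to 0.29 SD for assumed T0–T2 correlations of 0.5 to 0.7 and the caveat that T0 in period II may already reflect the intervention.

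If the post-period figure of about 0.29 SD is also quoted, it should be labelled as such, with the statement that it leaves any standing difference between the hospices in the estimate.

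The cost is a rewritten paragraph. T0 is already collected and no extra patients are needed. The price is a less favourable stated precision.

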**Methods:**

The intervention will be evaluated through a quasi-experimental non-equivalent comparison group before-after study design. This project can be classified as phases 1–2, according to the Medical Research Council (MRC) framework for the development and evaluation of complex interventions.

The study setting will take place in two inpatient hospice units in Italy. The study sample will be constituted of 39 multidisciplinary healthcare professionals and a sample of 46 advanced cancer patients admitted to hospices during the implementation of the intervention.

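### The stated precision is wrong: 17 patients per group puts the one-sided 80% limit about 0.29 SD from the difference, not 0.200

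*Protocol article*

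**What the plan says.** The Sample size section of the protocol article sizes the pilot by a confidence-limit rule. If the observed difference is zero, "then the upper confidence limit will exclude the estimate that is considered “clinically significant” in the planned definitive trial". The target and the confidence level follow: "We will consider a small effect size of 0.3 and choose a confidence of 80" per cent.

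The size chosen is given as "A sample size of 17 patients for unit/period". According to the section, the limit of a one-sided 80% interval for the difference between two means then lies at a distance "equal to 0.200 when the estimated standard deviations are 1.00 and 1.00". For 30% attrition, the section adds patients, which "will lead to the inclusion of 6 additional patients for a total of 23 patients unit/period". The Abstract (Methods) gives "a sample of 46 advanced cancer patients admitted to hospices during the implementation of the intervention", which is 2 × 23, that is, two groups.

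**The concern.** The sentence contains everything needed to check it: the group size, the confidence level, the sidedness and both SDs. The distance it reports does not follow from them. It is also not the distance that the section's own aim leads to, since the effect to be excluded is 0.3.

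This distance is the only quantitative precision claimed for the pilot. The section ties the 80% level to decisions about the later trial, and the article says the study will inform the sample size and power of phase 3. Anyone relying on 0.200 would treat effects between 0.20 and 0.29 SD as ruled out by a null pilot when they are not. Conversely, a reader who took 0.200 as the design target would conclude that the pilot has fewer than half the patients it needs.

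**Working it through.** **Inputs, all from the Sample size section**

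- Evaluable patients: 17 per unit and period
- SD: 1.00 in each of two groups
- Confidence: 80%, one-sided
- Effect to be excluded when the observed difference is zero: 0.3

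**Formula.** For the difference of two independent means, the distance to the one-sided limit is

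d = q × SD × √(1/n + 1/n)

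where q is the 80% quantile of t with 2n − 2 degrees of freedom, or of the standard normal.

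**Attempt to reproduce 0.200**

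- √(2/17) = 0.343
- t version: q = 0.853 (32 df), so d = 0.853 × 0.343 = **0.293**
- Normal version: q = 0.8416, so d = 0.8416 × 0.343 = **0.289**

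The printed 0.200 is not reproduced. The ratio is 0.293/0.200 = 1.46.

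**What 0.200 would require, changing one input at a time**

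- Group size: the normal version gives n = 2 × (0.8416/0.2)² = 35.4, so 36. The t version also gives 36 (d = 0.1996).
- Confidence: 0.200/0.343 = 0.583, and P(t with 32 df < 0.583) = 0.718, so about 72% rather than 80%.
- SD: 0.200/0.293 = 0.68 rather than 1.00.

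**What the target of 0.3 requires**

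| n per group | t-based d | normal d |
|---|---|---|
| 16 | 0.302 | 0.298 |
| 17 | 0.293 | 0.289 |

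With t, 17 is the first group size below 0.3. With the normal quantile, 16 would already do.

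**Other readings of the sentence**

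| Reading | normal d | t-based d |
|---|---|---|
| Two-sided 80%, 17 per group | 0.440 | 0.449 |
| 23 per group (before attrition) | 0.248 | 0.251 |
| One sample of 17 | 0.204 | 0.210 |
| Both periods pooled, 34 per unit | 0.204 | 0.205 |
| Four-cell before/after, between-unit contrast, 17 per cell | 0.408 | 0.411 |

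None gives 0.200. The two nearest still miss a figure printed to three decimals, and neither fits the text. A single sample has no difference in means with two SDs. Pooling contradicts a size given per unit and period, and would mix pre-test patients with those treated after the intervention began.

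**The case against.** The strongest reply is that the slip has no practical effect. The true limit of 0.293 is below 0.3, so the section's own rule is met with 17 per group; recruitment and procedures stay the same, and 0.200 is not used again. On this view it is a misreported descriptive figure, perhaps a misprint for 0.300, in a pilot concerned mainly with feasibility. It is true that n survives. But the printed number still overstates the precision of the design, and it is the only such figure given. The misprint explanation is plausible but is not stated in the document.

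A second point is that 0.200 does not strictly conflict with the target, because a limit at 0.200 would also exclude 0.3. That is right: the arithmetic conflict is with n = 17 and SD 1.00. Against the target, the point is only that 0.200 is not the distance that leads to 17, whereas 0.3 is.

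A third point is that the document does not say which number was intended. If 0.200 was, 36 evaluable patients per unit and period would be needed. The match between 17 and 0.3 makes this unlikely but does not exclude it.

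Finally, the design is before/after with a comparison unit. If the intended contrast were a difference in differences, the distance would be about 0.41 and 0.3 would not be excluded. The article does not name that contrast in the sample-size calculation, so this is an assumption. It is a reason to limit the corrected statement to the two-group comparison that the sentence describes.

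**Conclusion.** The stated distance is wrong. With the section's own inputs it is 0.293 (t, 32 df) or 0.289 (normal), not 0.200, so the true distance is about 46% wider than printed. The group size of 17 is consistent with excluding 0.3 SD, and the printed distance is the figure to correct.

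The result assumes independent patients, equal groups of 17 evaluable patients, SD 1.00 in each, and a simple comparison of two means. That the distance rather than n is at fault is an inference from the exact t-based match between 17 and 0.3.

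**What to change.** In the Sample size section, replace 0.200 with 0.293, or with wording such as just under 0.30. Add that the criterion met is exclusion of an effect of 0.3 SD, given an observed difference of zero, in a simple two-group comparison with one-sided 80% confidence. Keep 17 evaluable patients per unit and period.

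The cost is one number and a clause. The stated precision becomes less favourable, and no more patients are needed. The sponsor should confirm that 0.3 was the intended target; only if 0.200 was truly meant would the evaluable group size have to rise to 36.

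### The 30% attrition allowance is applied to the 17 completers needed, not to those enrolled, so 23 per unit/period leaves about 16 and covers at most 26% attrition

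*Protocol article*

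**What the plan says.** The Sample size section of the protocol article builds its figure in three steps.

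- **Target.** If the observed difference is zero, the upper confidence limit should exclude the effect regarded as clinically significant: "We will consider a small effect size of 0.3 and choose a confidence of 80" per cent.
- **Base number.** "A sample size of 17 patients for unit/period produces a one-sided 80% confidence interval", with a distance from the mean difference to the limit "that is equal to 0.200 when the estimated standard deviations are 1.00 and 1.00".
- **Attrition.** "A 30% attrition rate based on rates identified in a recent systematic review" is then said to bring six extra patients: it "will lead to the inclusion of 6 additional patients for a total of 23 patients unit/period".

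The Methods part of the abstract gives "a sample of 46 advanced cancer patients admitted to hospices during the implementation of the intervention", which is 2 × 23.

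**The concern.** An attrition allowance should leave the required number after losses. The losses come out of everyone enrolled, so the required number is divided by the proportion retained. Here the rate seems to have been multiplied by the required number and the product added. That always gives too few, and the gap widens as the rate rises.

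At stake is whether 23 per unit/period delivers the 17 on which the precision statement rests. The section on operational definitions also makes piloting the sample size for a phase 3 trial a secondary objective, so the same step could be carried into the larger trial.

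**Working it through.** **Inputs (all from the Sample size section).** Required n = 17 per unit/period; attrition d = 30%; enrolled N = 23 (17 + 6); effect to exclude 0.3; one-sided 80% confidence; SD 1.00 in each group; stated distance 0.200.

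**1. Reproducing the plan's figure.** Using n × d: 17 × 0.30 = 5.1, rounded up to 6, and 17 + 6 = 23. Equivalently, n × (1 + d) = 17 × 1.3 = 22.1, rounded up to 23. The stated figure is matched exactly, and nothing else in the article gives another origin for the 6.

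**2. What 23 delivers.** Expected completers N × (1 − d) = 23 × 0.70 = 16.1, against 17 required. The attrition at which 17 remain is 1 − 17/23 = 6/23 = 26.1%.

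**3. Enrolment that keeps 17 at 30%.** n/(1 − d) = 17/0.70 = 24.3, rounded up to 25. Check: 24 × 0.70 = 16.8, still short; 25 × 0.70 = 17.5.

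| | Stated | 17 kept at 30% attrition |
|---|---|---|
| Extra patients per unit/period | 6 | 8 |
| Enrolled per unit/period | 23 | 25 |
| Expected completers | 16.1 | 17.5 |
| Two unit/periods | 46 | 50 |
| Four unit/periods | 92 | 100 |

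**4. Effect on precision.** The distance to the one-sided 80% limit for two groups of n with SD 1 is q × √(2/n). Here q is the 80% quantile, from the normal distribution (z) or from t with 2n − 2 degrees of freedom.

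| n per group | z | t |
|---|---|---|
| 16 | 0.298 | 0.302 |
| 17 | 0.289 | 0.293 |
| 36 | 0.198 | 0.200 |

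By t, 17 is the smallest n with a distance below 0.3. By z, 16 is enough: 2 × (0.8416/0.3)² = 15.7.

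**5. The stated 0.200.** Two groups of 17 with SD 1.00 give about 0.29, not 0.200. A distance of 0.200 needs about 36 per group: 2 × (0.8416/0.2)² = 35.4 by z. Pooling both periods to 34 per group comes close (0.204 by z), but the text attaches 0.200 to 17 per unit/period.

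**The case against.** Several points against making much of this have force.

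- **The criterion is not shown to fail.** A reader might infer that at the plan's own attrition rate the pilot no longer excludes 0.3. That rests on 0.302 against 0.3 under a t quantile. The section names neither t nor z, and by z the limit at 16 is 0.298, which does exclude 0.3. The document supports borderline, not failed.
- **A joint probability would mislead.** With independent 30% dropout, the chance that a cell of 23 keeps at least 17 is 0.44, and a reader might raise this to the fourth power for all four cells (0.44⁴ ≈ 0.04). The plan never requires every cell to keep 17. On the same model, 25 per cell gives 0.68 per cell and only 0.677⁴ ≈ 0.21 for all four. Both inflation formulas aim at expected completers, so this figure does not measure the error.
- **The practical effect is small.** Under Study population, all newly admitted adult cancer patients are to be invited over two fixed three-month periods, and nothing says that recruitment stops at 23. Patient dropout is itself an outcome under Feasibility of the study. The shortfall is about one completer per cell.
- **25 is conditional.** It is right only if 17 stands, and the 0.200 attached to 17 does not reproduce.

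One defence fails. A z-based requirement of 16 would inflate correctly to 23 (16/0.70 = 22.9), but the text states 17 plus 6. None of these points makes 23 the result of 17 with 30% attrition.

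**Conclusion.** The point holds as a minor arithmetic error that is wrong as written. At the stated 30% attrition, 23 enrolled leaves 16.1 expected completers per unit/period, about one below the stated 17, and 23 covers at most 26% attrition. Keeping 17 takes 25, two more per unit/period.

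This rests on reading 17 as the number needed after attrition, which is the only reading under which an attrition allowance is added to it, and on taking the 30% as given. The shortfall against 17 does not depend on the choice of quantile. The effect on the 0.3 target does, and amounts to a limit of about 0.30. The documents do not support a claim that the pilot's decision rule breaks down.

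**What to change.** Edit the Sample size section in one of two ways.

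1. **Keep 23.** State that 23 per unit/period yields about 16 expected completers at 30% attrition, with a one-sided 80% distance of about 0.30, and keeps 17 only if attrition is at most 26%. The abstract's 46 then stands. Cost: none beyond the wording.
2. **Keep 17 completers.** Give 17/0.70 = 24.3, so 25 per unit/period (8 additional patients), and change the abstract's 46 to 50. Cost: two more patients per unit/period, eight over all four.

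With either choice, correct the distance of 0.200 at 17 per unit/period to about 0.29 in the same edit, and say whether t or z was used (0.293 or 0.289). Otherwise option 1 would set 0.30 at 16 completers beside 0.200 at 17, a new contradiction. If 0.200 was the intended precision, the base number of 17 has to be reopened before any attrition allowance is applied, and 25 no longer follows.
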